# Robotic-assisted Esophagectomy vs Video-Assisted Thoracoscopic Esophagectomy (REVATE): study protocol for a randomized controlled trial

**DOI:** 10.1186/s13063-019-3441-1

**Published:** 2019-06-10

**Keywords:** Esophageal cancer, Robotic esophagectomy, Thoracoscopic esophagectomy, Recurrent laryngeal nerve, Lymph node dissection

## Abstract

**Background:**

Radical lymph node dissection (LND) along the left recurrent laryngeal nerve (RLN) is surgically demanding and can be associated with substantial postoperative morbidity. The question of whether robot-assisted esophagectomy (RE) might be superior to video-assisted thoracoscopic esophagectomy (VATE) for performing LND along the RLN in patients with esophageal squamous cell carcinoma (ESCC) remains open.

**Methods/design:**

We will conduct a multicenter, open-label, randomized controlled trial (Robotic-assisted Esophagectomy vs Video-Assisted Thoracoscopic Esophagectomy (REVATE)) enrolling patients with ESCC scheduled to undergo LND along the RLN. Patients will be randomly assigned to either RE or VATE. The primary outcome measure will be the rate of unsuccessful LND along the left RLN, which will be defined as: failure to remove lymph nodes along the left RLN (i.e., no identifiable nodes on pathology reports); or occurrence of permanent (duration > 6 months) left RLN palsy following LND. Secondary outcomes will include the number of successfully removed RLN nodes, postoperative recovery, length of hospital stay, 30-day and 90-day mortality, quality of life, and oncological outcomes.

**Discussion:**

The REVATE study provides an opportunity to explore whether RE could facilitate LND along the left RLN—a complex surgical procedure that, as of now and with the use of VATE, remains difficult to perform and associated with a significant burden of morbidity.

**Trial registration:**

ClinicalTrials.gov, NCT03713749. Registered on 22 October 2018.

**Electronic supplementary material:**

The online version of this article (10.1186/s13063-019-3441-1) contains supplementary material, which is available to authorized users.

## Background

Metastases to nodes located around the recurrent laryngeal nerve (RLN) occur commonly in patients with esophageal squamous cell carcinoma (ESCC), especially when tumors are located in the middle or the upper third of the esophagus [1–4]. Lymph node dissection (LND) along the RLN is considered beneficial in patients with esophageal cancer because it can result in more accurate disease staging as well as improved local control rates. However, RLN LND is surgically demanding and is frequently complicated by RLN palsy (occurrence rate 20–80%)—which is especially common on the left side [5, 6]. Injury of the RLN induces a paresis or palsy of the vocal cords—which can in turn increase the rates of postoperative pulmonary complications and severely impair quality of life [7–9].

Owing to an improved magnification, the significant advances made in video-assisted thoracoscopic esophagectomy (VATE) over the last decades have led to significant improvements in surgical results [10]. Compared with open surgery, experienced surgical teams may obtain a significant reduction of postoperative complications through the use of VATE [10–12]. Unfortunately, RLN LND remains challenging even in the VATE era—especially on the left side—mainly because of major technical barriers (e.g., limited surgical space, rigidity of the instrumentation, two-dimensional vision) [13]. Importantly, a previous study has shown that VATE is unable to reduce the rates of postoperative RLN palsy following RLN LND [14].

Currently, robotic surgery with three-dimensional stereoscopic 10× magnified visualization systems and flexible wrist mechanisms is a leading technology to improve the accuracy of dissections performed in limited anatomical spaces. Although interest in robot-assisted esophagectomy (RE) is growing [15–17], there are limited studies comparing the robotic approach with VATE [18–20]. Specifically, the question of whether RE might be superior to VATE for performing LND along the RLN in patients with ESCC remains open.

The REVATE study aims to assess the efficacy and safety of RE to perform RLN LND in patients with ESCC. The primary hypothesis is that—compared with VATE (REVATE control group)—the use of RE (REVATE treatment group) can reduce the rate of unsuccessful LND along the left RLN, which will be defined as: failure to remove lymph nodes along the left RLN; or occurrence of permanent left RLN palsy following LND. Secondary objectives are to evaluate the impact of RE on the following variables: number of successfully removed RLN nodes, postoperative recovery, length of hospital stay, 30-day and 90-day mortality, quality of life, and oncological outcomes.

## Methods/design

### Design and setting

A study flowchart is shown in Fig. 1. This is an investigator-initiated, investigator-driven multicenter, open-label, randomized controlled trial (termed REVATE) enrolling patients with ESCC scheduled to undergo LND along the RLN. Patients will be randomly assigned (1:1 ratio) to undergo minimally invasive esophagectomy (MIE) with either RE or VATE. All participating surgeons will be required to have competence with both techniques. The study will take place in two high-volume surgical centers located in Taiwan and China, and will be conducted with adherence to the principles of the World Medical Association’s Declaration of Helsinki.

**Fig. 1 Fig1:**
[figure not shown]
Robotic-assisted Esophagectomy vs Video-Assisted Thoracoscopic Esophagectomy (REVATE) study flowchart. LND lymph node dissection, RLN recurrent laryngeal nerve

### Study population: inclusion and exclusion criteria

Our study population will consist of adult patients with ESCC requiring MIE. Inclusion criteria will be as follows: age between 18 and 80 years; histology-proven primary intrathoracic ESCC; scheduled treatment with MIE (McKeown procedure) and bilateral RLN LND; European Clinical Oncology Group performance status 0–1; presence of surgically resectable disease (cT1−4a, N0–3, M0) defined according to the *American Joint Committee on Cancer (AJCC) Staging Manual*, eighth edition [21]; normal bilateral vocal cord function confirmed by preoperative laryngoscopic examination; and willingness to provide written informed consent. If the candidates meet any of the following criteria, they will not be eligible for the study: history of previous major thoracic surgery that renders MIE unfeasible; malignancies different from ESCC; and inability to undergo curative resection and/or to comply with the follow-up schedule.

### Timeline of inclusion and randomization

Patients who do not require preoperative neoadjuvant chemoradiotherapy (nCRT) will be informed about potential inclusion in the first 3 weeks of the study before the scheduled operation. When nCRT will be necessary, candidates will be approached only upon completion of the nCRT course.

### Randomization

A computerized randomization tool will be used to randomly allocate patients to either RE or VATE (1:1 ratio). In order to minimize the potential confounding effect of local treatment variables (e.g., postoperative care), patients will be stratified in a 1:1 fashion according to the enrolling hospital. A permuted-block randomization with varying block size will be implemented. Allocation and block size will be concealed from all investigators. Blinding of surgeons is unfeasible because of the obvious technical differences between RE and VATE. However, the occurrence of the study endpoints will be determined from medical records by an independent assessor who will be blinded to the surgical technique used for each case. Patients will have the option to withdraw from the study at any time.

### Surgical approach

Regardless of the treatment arm (i.e., RE versus VATE), all patients will undergo a total two-field lymphadenectomy according to the consensus proposed in 1994 by the International Society of Disease of Esophagus (ISDE) [22]. The operating surgeon will be exempted from performing RLN LND in the presence of at least one of the following conditions: low surgical curability as evidenced by tumor ingrowth into adjacent organs (i.e., T4b status) or unexpected detection of distant metastases (i.e., M1 status) during surgery; and/or occurrence of previously unforeseen perioperative adverse events and/or findings which will require discontinuation of surgery (all of these events will be detailed on an individual basis). Other surgical variables—including the use of laparotomy versus laparoscopy, the technique used for anastomosis, and the route of reconstruction—are not expected to influence the results of RLN LND and will be left to the surgeon’s discretion.

### Definition of RLN lymph nodes

The location of bilateral RLN lymph nodes will be defined according to the criteria proposed by the Japan Esophageal Society (JES) [23]. Right (station 106recR) and left (station 106recL) RLN lymph nodes correspond, respectively, to stations termed 2R and 2L in the *AJCC Staging Manual*, eighth edition (Table 1).

**Table 1 Tab1:** Comparisons of the nomenclature and grouping of mediastinal lymph nodes as proposed by the AJCC/UICC and JES systems for patients with esophageal cancer

AJCC/UICC system	JES system
Station 2R: upper right paratracheal lymph nodes	Station 106recR: right recurrent laryngeal nerve nodes
Station 2L: upper left paratracheal lymph nodes	Station 106recL: left recurrent laryngeal nerve nodes
Station 8U: upper thoracic paraesophageal lymph nodes	Station 105: upper thoracic paraesophageal lymph nodes
Station 4R: right lower paratracheal lymph nodes	Station 106pre: pretracheal lymph nodes
	Station 106tbR: right tracheobronchial lymph nodes
Station 4L: left lower paratracheal lymph nodes	Station 106tbL: left tracheobronchial lymph nodes
N/A	Station 113: ligamentum arteriosum lymph nodes
N/A	Station 114: anterior mediastinal lymph nodes
Station 7: subcarinal lymph nodes	Station 107: subcarinal lymph nodes

*AJCC* American Joint Committee of Cancer, *UICC* Union for International Cancer Control, *JES* Japan Esophageal Society, *N/A* not available

### Data collection and management

At inclusion, an unequivocal identification code will be generated for each participant, with its access being restricted to the principal investigator (PI) and the study coordinators. A good clinical practice (GCP)-compliant digital case record form (CRF) will be used for data collection, for which the study coordinators and/or research nurses will be in charge. Nonelectronic data will be secured in locked cabinets located at data coordinating centers, being accessible to the PI, as well as research nurses and physicians. Each participating center will be allowed to request information from the principal database, but direct access will be permitted only for locally generated data. Upon termination of the study, data access requests may be forwarded to the PI. The completed CRFs will be cross-checked with the original sources to ensure that data regarding the primary and secondary outcome measures will be accurate and reliable. All clinical records will be stored anonymously to protect privacy and all investigators will adhere to local confidentiality regulations.

### Primary outcome measure

The primary outcome measure will be the rate of unsuccessful LND along the left RLN, which will be defined as: failure to remove lymph nodes along the left RLN (i.e., no identifiable lymph nodes confirmed by pathology reports); or occurrence of permanent (duration > 6 months) left RLN palsy following LND. Regardless of the presence of hoarseness, vocal cord function will be assessed by an experienced otolaryngologist using a flexible laryngoscope within 1 week of surgery. RLN palsy will be classified according to the following variables: site (unilateral versus bilateral); duration (temporary (i.e., recovering within 6 months) versus permanent (i.e., not recovering within 6 months)); and type of treatment required (type I, no therapy required; type II, injury requiring an elective surgical procedure; type III, injury requiring an urgent surgical procedure) [24]. All patients diagnosed with postoperative RLN palsy will undergo additional laryngoscopic examinations at 1, 3, and 6 postoperative months to confirm the occurrence of permanent RLN palsy (defined as its persistence at 6 months after surgery).

### Secondary endpoints

Secondary endpoints will include: the number of nodes removed along the right and left RLN; the incidence of pneumonia, defined according to the Revised Uniform Pneumonia Score which includes temperature, leukocyte count, and pulmonary radiography (Table 2) [25]; the incidence of other postoperative complications (e.g., anastomotic leakage, chylothorax), defined according to the Esophagectomy Complications Consensus Group system; the total percentage of surgery-related major postoperative complications (i.e., grade IIIa or higher according to the Clavien–Dindo criteria) [26]; in-hospital, 30-day, and 90-day mortality rates, defined as any death occurring during the same hospitalization and within 30 or 90 days after surgery, respectively; R0 resection rates, defined as microscopically negative proximal/distal and circumferential margins; surgery-related parameters (including thoracic, abdominal, and total surgical time (expressed in minutes); unexpected events and complications occurring during surgery (e.g., massive hemorrhage, perforation of other organs); blood loss during surgery (expressed in milliliters per phase); and number of patients requiring conversion to thoracotomy and related reasons); postoperative recovery parameters (including length of mechanical ventilator use after surgery (expressed in minutes), length of ICU stay (expressed in hours), length of hospital stay (expressed in days), and need for reintubation or readmission to the ICU); quality of life and psychometric measures (including the EORTC QLQ-C30, OES-18, and Hospital Anxiety and Depression Scale (HADS) questionnaires, administered at the following time points: 5 days before surgery; 4 weeks, 3 months, and 6 months after surgery; and on a yearly basis up to 5 years thereafter); and oncological outcomes (including 2-year, 3-year, and 5-year disease-free and overall survival rates).

**Table 2 Tab2:** Revised Uniform Pneumonia Score

Diagnostic criterion	Revised Uniform Pneumonia Score	
	Range	Score
Temperature (°C)	≥ 36.1 and ≤ 38.4	0
	≤ 36.0 and ≥ 38.5	1
Leukocyte count (× 10^9^/L)	≥ 4.0 and ≤ 11.0	0
	< 4.0 or > 11.0	1
Pulmonary radiography	No infiltrate	0
	Diffused (or patchy) infiltrate	1
	Well-circumscribed infiltrate	2

A sum score of 2 points or higher, in which at least 1 point is assigned because of infiltrative findings on pulmonary radiography, indicates the presence of pneumonia

### Quality control

In order to avoid a learning curve bias, only surgeons with a proven track of at least 50 previously performed RE and VATE procedures will be involved in the trial. Every operation performed within the trial will be video-recorded. All of the events of interest (related to the study outcomes) and surgical videos will be regularly reviewed by a local independent committee consisting of surgeons with proven expertise in MIE and involved in the conduct of the trial. All disagreements will be handled by a senior member of the Upper GI International Robotic Association (http://ugira.org/)—whose decision will be final.

### Follow-up schedule

Randomization will be considered the start of the study for each participant. All patients will be followed up according to the schedule shown in Fig. 2. The primary study endpoint will be assessed at 1 week (in the entire study cohort) and 6 months (in the subgroup of patients with confirmed postoperative left side RLN palsy at 1 postsurgical week). Data on postoperative complications, readmissions, and deaths occurring within 30 and 90 postoperative days will be collected. The study visits are planned at the following time points: 2 weeks before surgery; 4 weeks, 3 months, and 6 months after surgery; and every 6 months thereafter (until 5 postoperative years).

**Fig. 2 Fig2:**
[figure not shown]
Standard Protocol Items: Recommendations for Interventional Trials (SPIRIT) schedule of patient enrolment, interventions, and assessments

### Recruitment and trial timeline

The study started on November 12, 2018, with a projected 3-year inclusion period. Analysis of short-term results and long-term oncological outcomes will be conducted at 6 months and 5 years after discharge of the last randomized patient, respectively. The expected total duration of the trial is 8 years, including prearrangement and data analysis. The investigators will release interim reports at the end of each preplanned follow-up period.

### Sample size calculation

Based on a preliminary study conducted by our group, the projected rates of successful left RLN LND (according to the definition proposed in the current trial) are 70–75% and 85–90% for VATE and RE, respectively [20]. The purpose of our study is to demonstrate that the rate of successful left RLN LND will be at least 15% higher for RE compared with VATE (based on a conservative 75% rate for VATE). Because our null hypothesis is that the difference between the two arms is ≤15%, we will adopt one-sided testing. In a one-sided test, the “extreme” portion of distribution is decided beforehand as meaning “sufficiently large” (i.e., 15% in our case) [20]. Assuming an alpha error of 0.05 and an 80% power using one-sided two-sample comparisons of proportions under a balanced trial design, a total of 95 patients per treatment arm will be required. Assuming a dropout rate of 10% in the entire study cohort, we plan to enroll a total of 212 patients (i.e., 106 in each arm).

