### Statistical analysis

A formal statistical analysis plan will be prepared by both an independent statistician and the principle investigator ahead of the final data collection (both blinded to treatment allocation and the study results). The final study findings will be released by the study statistician. Data analysis will be performed in patients who will receive RLN LND according to the procedure assigned at randomization and who will have complete follow-up data on nerve palsy recovery status at the 6-month assessment (for confirmation of permanent nerve palsy). A small percentage of patients (estimated 5% maximum) are expected not to undergo the procedure assigned at randomization either because of self-withdraw from the study or because of occurrence of unexpected intraoperative findings (as described in the “Surgical approach” section). Another 5% of patients may potentially be lost to follow-up, resulting in a maximum expected total dropout rate of 10%. We will perform both an in-depth analysis of the reasons for dropout and a comparison of dropouts and completers. The primary outcome will be analyzed using a two-sample proportion test (single-sided). Categorical secondary outcomes will be expressed as frequencies and compared with the Fisher’s exact test. Continuous secondary outcomes will be given as means ± standard deviations (for normally distributed variables) or medians and interquartile ranges (for skewed parameters). Comparisons will be performed using Student’s *t* test and the nonparametric Mann–Whitney *U* test, respectively. The Cochran–Mantel–Haenszel test will be used to examine the differences in categorical outcomes between the two treatment groups after adjusting for study center and use of nCRT. All calculations will be conducted with SAS (version 9.3; SAS Institute Inc., Cary, NC, USA) and SPSS (version 20.0; SPSS Inc., Chicago, IL, USA) statistical packages. *P* < 0.05 will be considered statistically significant.

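### The sample size section uses 15 points both as the null boundary and as the assumed true effect; 95 per arm fits only an ordinary superiority test with a null of zero

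*Protocol article*

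**What the plan says.** The Sample size calculation section gives the projected success rates, which "are 70–75% and 85–90% for VATE and RE, respectively", and says the comparison is "based on a conservative 75% rate for VATE". It states the aim as to "demonstrate that the rate of successful left RLN LND will be at least 15% higher for RE compared with VATE". It then sets the null and takes the direction of the test from it: "Because our null hypothesis is that the difference between the two arms is ≤15%, we will adopt one-sided testing". The next sentence describes 15% as the threshold for a sufficiently large result. The size follows: "Assuming an alpha error of 0.05 and an 80% power using one-sided two-sample comparisons of proportions", giving 95 per arm, raised to 106 per arm (212 in total) for 10% dropout.

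Elsewhere the protocol has no 15-point margin. The primary hypothesis at the end of the Background is that RE "can reduce the rate of unsuccessful LND along the left RLN". The Statistical analysis section says: "The primary outcome will be analyzed using a two-sample proportion test (single-sided". The Interim analysis section describes the efficacy rule as a better outcome with RE, and futility as no difference between the arms.

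**The concern.** A margin that must be exceeded and an effect assumed for power are different quantities. If the trial must rule out differences of 15 points or less, the true difference has to be well above 15 points for the trial to have useful power. If 15 points is the expected effect, the null has to sit below it, ordinarily at zero. The section gives both roles to one number.

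What is at stake is the meaning of the primary result. The protocol carries two primary hypotheses, and there is a wide band of results in which one is met and the other is not. A significant ordinary test could also be reported, in line with the stated aim, as showing a gain of at least 15 points that the data do not establish. The reason given for one-sided testing rests on the same confusion.

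**Working it through.** **Inputs** (Sample size calculation section): VATE 70–75%, RE 85–90%, one-sided alpha 0.05 (z = 1.645), power 80% (z = 0.842), equal arms, 95 evaluable per arm, 10% dropout.

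**1. Reproducing 95 per arm, null difference 0.**
n = [1.645·√(2p̄q̄) + 0.842·√(p₁q₁ + p₂q₂)]² / (p₂ − p₁)²

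- 70% vs 85%: p̄ = 0.775, 2p̄q̄ = 0.34875, p₁q₁ + p₂q₂ = 0.21 + 0.1275 = 0.3375. This gives n = 94.8, so 95 per arm, with power 80.1%. Dropout: 95/0.9 = 105.6, so 106 per arm and 212 in total. Both stated figures are matched.
- 75% vs 90%: 79 per arm (92 with continuity correction). At 95 per arm the power is 86%.

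The plan's figure is therefore a zero-null calculation. It matches 70% vs 85% and not the 75% control rate named in the text. That is a separate discrepancy and does not affect this point.

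**2. Power against the null as written (difference ≤ 0.15).**
Power = Φ[(d − 0.15)/SE − 1.645], SE = √[(p₁q₁ + p₂q₂)/95]

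| VATE vs RE | True difference | Power at 95 per arm |
|---|---|---|
| 75% vs 85% | 10 points | 0.6% |
| 70% vs 85% | 15 points | 5.0% |
| 75% vs 90% | 15 points | 5.0% |
| 70% vs 90% | 20 points | 22.5% |

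For the last row, SE = √(0.30/95) = 0.0562 and Φ(0.05/0.0562 − 1.645) = 0.225. Exact binomial enumeration gives 5.1% (75/90), 5.3% (70/85) and 23.1% (70/90). When d = 0.15 the first term is zero, so power equals alpha at any sample size. For 80% power at 70% vs 90%, n = (1.645 + 0.842)² × 0.30 / 0.05² ≈ 742 per arm.

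**3. What an observed result would show.** Take 71/95 successes (74.7%) on VATE.

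- Ordinary test, null 0: the smallest significant RE result is 81/95 (85.3%), a gap of 10/95 = 10.5 points. Pooled SE = √(2 × 0.8 × 0.2/95) = 0.0580 and z = 0.1053/0.0580 = 1.81. The one-sided 95% lower bound, with unpooled SE 0.0575, is 0.105 − 1.645 × 0.0575 ≈ 0.011, about 1 point.
- Null ≤ 0.15: the smallest significant RE result is 93/95 (97.9%), a gap of 22/95 = 23.2 points.

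Observed gaps from about 10.5 points to just under 23 points count as success under one reading and failure under the other. The planned 15-point effect lies inside that band.

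**The case against.** The strongest defence is that the plan does not specify the test to which the 5% applies. The primary hypothesis, the named test, the interim rule and the sample size all describe ordinary superiority, and only the sentences on the null and the aim dissent. Under that test the one-sided 0.05 error rate against a null of zero is as stated, and power is 80% at 70% vs 85% and 86% at 75% vs 90%. A formal analysis plan is also announced, which could state the hypothesis properly.

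Most of this stands. A reader might infer that the trial really has 5% power, or will almost surely fail if RE performs as projected. The documents do not support that: the 5% holds only if the literal null is tested and the true difference is exactly 15 points, and one projected pair gives about 23%. Nor do they support the inference that 95 per arm is too few for the hypothesis in the Background.

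What does not stand is leaving the sentences for a later document to put right. They are not an omitted detail. They state a null and a claim that the design cannot deliver, and an analysis plan would have to contradict them.

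**Conclusion.** The point holds as an error in the stated hypothesis and in the claim built on it, not as a shortfall in enrolment. Whichever test is run, the design does not offer 80% power to show a gain of more than 15 points: testing the written null gives at most about 23% power within the projected ranges, and the ordinary test does not address that claim. These figures assume 95 evaluable patients per arm, a one-sided 0.05 level, and a normal approximation that exact enumeration confirms.

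A reader might also infer that one-sided 0.05 must now give way to one-sided 0.025. That does not follow. The reason given for one-sidedness fails, but the level is a separate choice with a price: at 95 evaluable per arm, one-sided 0.025 gives 78% power under 75% vs 90% but only 70% under 70% vs 85%, the pair that yields 95.

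**What to change.** In the Sample size calculation section:

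- State H0: p(RE) − p(VATE) ≤ 0 against H1: p(RE) − p(VATE) > 0, where p is the rate of successful left RLN dissection.
- Describe 15 points as the difference assumed for power, not as a margin to be ruled out.
- Reword the aim as showing that the success rate is higher with RE.
- Delete the two sentences that derive one-sided testing from the 15-point null. If one-sided testing is kept, justify it in its own right.
- Report the difference in success rates with a confidence interval, so that readers can see how far the data support a gain of any given size.

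The cost is a wording amendment with no added patients and no change to the named test. The claim weakens from superiority by at least 15 points to superiority. It should be settled before outcome data by arm could influence the choice of null.

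If a 15-point margin really is intended, rewording is not enough. The margin must be written into the test and the trial re-sized: about 742 per arm at 70% vs 90%, and no sample size suffices if the true difference is 15 points.

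### The 95 patients per arm do not follow from the stated 75% VATE success rate; they match 70% versus 85%, while 75% versus 90% needs 79

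*Protocol article*

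**What the plan says.** The section Sample size calculation in the protocol article first gives projected rates of successful left RLN dissection, which "are 70–75% and 85–90% for VATE and RE, respectively". It then sets the aim of showing that "the rate of successful left RLN LND will be at least 15% higher for RE compared with VATE", with the calculation "based on a conservative 75% rate for VATE". A 15-point gain on 75% puts RE at 90%.

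The remaining inputs are in the same section: "Assuming an alpha error of 0.05 and an 80% power", "using one-sided two-sample comparisons of proportions under a balanced trial design". The result is that "under a balanced trial design, a total of 95 patients per treatment arm will be required", raised to 106 per arm (212 in total) for 10% dropout. The Statistical analysis section plans a matching test for the primary outcome, a one-sided two-sample proportion test, and mentions no continuity correction or exact method.

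**The concern.** Every input needed to recompute the sample size is in the text, so the result should reproduce, and it does not. The stated pair of rates needs clearly fewer than 95 per arm. A different pair, also within the projected ranges, gives 95 exactly.

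This paragraph is the only justification given for the size of the trial. As it stands, an ethics committee, the data safety monitoring committee or a reader cannot tell which success rates the 80% power belongs to. Nor can they tell whether the 16 extra patients per arm (95 − 79) reflect a slip, an unstated correction or another assumption. Anyone who re-estimates the sample size from 75% and 80% power starts from an inconsistent base.

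**Working it through.** **Inputs** (Sample size calculation): VATE 75%; gain 15 points; alpha 0.05, one-sided (z = 1.645); power 80% (z = 0.842); equal arms; dropout 10%. All figures below take a null hypothesis of zero difference.

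**Formula** (pooled variance under the null), per arm:

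n = [1.645 × √(2 p̄(1 − p̄)) + 0.842 × √(p₁(1 − p₁) + p₂(1 − p₂))]² / (p₂ − p₁)²

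**Step 1. Which pair of rates gives the plan's 95?** Take 70% versus 85%, so p̄ = 0.775:
- √(2 × 0.775 × 0.225) = 0.5906; × 1.645 = 0.971
- √(0.21 + 0.1275) = 0.5809; × 0.842 = 0.489
- n = (0.971 + 0.489)² / 0.0225 = 94.8, so **95**

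**Step 2. The rates the plan states.** Take 75% versus 90%, so p̄ = 0.825:
- √(2 × 0.825 × 0.175) = 0.5374; × 1.645 = 0.884
- √(0.1875 + 0.09) = 0.5268; × 0.842 = 0.443
- n = (0.884 + 0.443)² / 0.0225 = 78.3, so **79**

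**Step 3. Could another standard method turn 75% versus 90% into 95?**

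| Method, 80% power | 75% vs 90% | 70% vs 85% |
|---|---|---|
| One-sided, pooled | 79 | 95 |
| One-sided, unpooled | 77 | 93 |
| One-sided, arcsine | 76 | 94 |
| One-sided, pooled with continuity correction | 92 | 108 |
| Two-sided, pooled | 100 | 121 |
| Two-sided, unpooled | 97 | 118 |

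A one-sided Fisher exact test for 75% versus 90% has 79.6% power at 88 per arm, 80.7% at 90 and 82.7% at 95. No one-sided method tried gives 95 for 75% versus 90%. The nearest is the continuity-corrected 92. The two-sided results contradict the stated one-sided test and also miss 95. The mid-range pair, 72.5% versus 87.5%, gives 87 (one-sided, pooled).

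**Step 4. Power at 95 per arm.** Power = Φ{[(p₂ − p₁)√95 − 1.645 × √(2 p̄(1 − p̄))] / √(p₁(1 − p₁) + p₂(1 − p₂))}, and 0.15 × √95 = 1.462.
- 75% versus 90%: (1.462 − 0.884)/0.5268 = 1.098, so **86.4%** (exact binomial power of the same test: 87.3%)
- 70% versus 85%: (1.462 − 0.971)/0.5809 = 0.845, so **80.1%**

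**Step 5. Dropout.** 95/0.9 = 105.6, so 106 per arm and 212 in total. This step reproduces, so the fault lies before it.

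**Step 6. The word conservative.** With the gain fixed at 15 points, moving VATE from 70% to 75% lowers n from 95 to 79. Under the plan's own fixed gain, 75% is the less demanding assumption.

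**The case against.** The strongest reply is that nothing in the trial is harmed. At 95 per arm the study has at least 80% power against a zero difference for both 15-point scenarios, so the stated power is met or exceeded and enrolment need not change. This stands, and it makes the point a correction of the text, not of the design.

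Second, the article does not name the exact formula, and the full protocol is not shown. A continuity correction or an exact test narrows the gap from 16 patients per arm to between 3 and about 6. That is true, but neither gives 95, and the planned analysis mentions neither. That 70% versus 85% was the pair actually used is a strong inference from an exact match; the article does not say so.

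Third, 75% may be called conservative in another sense: it is the top of the VATE range, so it favours the comparator. If RE were held at 85%, raising VATE from 70% to 75% would raise n from 95 to 197; with RE at 90%, from 49 to 79. That reading is fair in general. It does not fit this section, which fixes the gain at 15 points, and it cannot produce 95 either. The 75% versus 85% case (53% power at 95 per arm) is a 10-point gain and has no bearing on whether 95 reproduces.

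**Conclusion.** The concern holds. With the inputs as stated, the planned test needs 79 per arm, so 95 is 16 patients per arm, or about 20% (16/79), too many for the stated 80% power. Either the VATE rate is misstated (70% and 85% give 95 exactly) or the power is (86.4% for 75% and 90%). The mismatch errs on the safe side and does not call the 212 into question.

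The conclusion rests on a one-sided test at 0.05, equal arms and a null of zero difference. The section also words its null as a difference of no more than 15 points. Under that null, a true 15-point gain would be rejected only at about the alpha rate, and none of these power figures would apply. That is a separate issue which this correction does not settle.

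**What to change.** Correct the sentence in Sample size calculation in one of two ways, according to what was actually calculated:

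- **(a)** State that 95 per arm is based on 70% for VATE and 85% for RE, one-sided alpha 0.05 and 80% power. This is the conservative pair for a fixed 15-point gain.
- **(b)** Keep 75% for VATE and 90% for RE, and state that 95 per arm gives about 86% power.

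In either case, stop describing the 75% rate as conservative, name the formula used, and say that the power is against a zero difference. Keep 106 per arm and 212 in total. The cost is one corrected sentence, with no change to enrolment.
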